## **XI - RIGHT TO ACCESS THE INFORMATION AND SOURCE DOCUMENTS**

Individuals with direct access in accordance with the legislative and regulatory provisions in force, in particular Articles L.1121-3 and R.5121-13 of the French Public Health Code (e.g., researchers, individuals in charge of quality control, monitors, clinical research assistants, auditors and all individuals collaborating in clinical trials) will take all the necessary precautions in order to ensure the confidentiality of the information related to the investigational medicinal products, trials, individuals taking part in the study and, in particular, any information involving their identity, as well as the results obtained. The data collected by these individuals through the course of quality controls or audits will then be made anonymous.

## **XII - LEGAL AND ETHICS ASPECTS**

The sponsor is defined by Law 2004-806 of 9 August 2004. AP-HP is the sponsor of this study and the Regional Delegation of Clinical Research (DRCD) undertakes the regulatory tasks.

Before beginning the study, each investigator must provide the sponsor's representative in the study with a signed and dated copy of their curriculum vitae, which must include their French National Medical Council registration number.

## **XII.1 - REQUEST FOR AUTHORISATION FROM THE AFSSAPS**

Before beginning the study, AP-HP, as the sponsor, must submit an authorisation request file to the competent authority (the AFSSAPS). The competent authority, as defined in Article L.1123-12, makes decisions related to the safety of individuals taking part in a biomedical research study, taking into account the safety and quality of the products used during the study in accordance with the regulations in force, where applicable, their condition of use and the safety of individuals with regard to procedures carried out and the methods used, as well as the planned methods of patient follow-up.

## **XII.2 - REQUEST FOR OPINION FROM THE ETHICS COMMITTEE**

In accordance with Article L.1123-6 of the French Public Health Code, the sponsor must submit the study protocol to an Ethics Committee. The committee's opinion will be reported to the competent authority by the sponsor before the study begins.

## **XII.3 - AMENDMENTS**

The DRCD must be informed of any planned changes to the protocol by the principal investigator.

Amendments must be classified as substantial or non-substantial. A substantial amendment is an amendment which may, in one way or another, change the guarantees given to the individuals taking part in the biomedical research (change in inclusion criteria, extension of enrolment period, participation of new sites, etc.).

Once the study has started, any substantial amendments proposed by the sponsor must receive a favourable opinion from the ethics committee and authorisation from the competent authority prior to being implemented. In this case, where necessary, the committee will ensure that a new consent form is duly collected from individuals taking part in the study.

Moreover, any extension to the study (radical change in the treatment regimen or populations included, extension of treatments and/or therapeutic procedures not originally foreseen in the protocol) must be considered as a new study.

Any substantial amendment must be submitted **by the sponsor** for authorisation from the AFSSAPS and/or for the ethics committee's opinion.

## **XII.4 - CNIL DECLARATION**

The law sets forth that the declaration of the electronic file with the personal data collected for the study must be prepared before the effective start of the study.

A reference methodology specific to the processing of personal data carried out in the context of biomedical research studies, defined by Law 2004-806 of 9 August 2004 as falling within

the scope of Articles L.1121-1 et seq. of the French Public Health Code, was established by the CNIL in January 2006. This methodology allows a simplified declaration procedure when the nature of the data collected in the study is consistent with the list provided by the CNIL in its reference document. When the protocol undergoes a quality control of the data by a CRA representing the sponsor and falls within the scope of the simplified CNIL procedure, the DRCD as the sponsor will ask the person in charge of the electronic file to undertake in writing to comply with the simplified MR06001 reference methodology.

#### **XII.5 - INFORMATION SHEET AND INFORMED CONSENT FORM**

Written consent must be collected from any individual taking part in the study before any procedures related to the biomedical research are performed.

Within the context of this study, the patients will be enrolled at the visit with the orthopaedist, the rheumatologist or the rehabilitation physician (enrolment visit). During this visit, the patient will be informed of all of the study-related information. At the end of the enrolment visit, if the patient meets all the eligibility criteria and agrees to participate in the study, he or she will provide the physician with the signed consent form.

#### **XII.6 - FINAL STUDY REPORT**

The final study report will be prepared by the principal investigator in collaboration with the biostatistician for this study. This report will be submitted to each of the investigators for their opinion. Once a consensus has been reached, the final version must be approved with the signature of each of the investigators and sent to the sponsor as soon as possible after the effective end of the study. A report prepared in accordance with the competent authority reference plan must be sent to the competent authority and to the ethics committee within one year after the end of the study, with the end of the study understood to be the last follow-up visit of the last subject enrolled. This period is set at 90 days if the study is terminated early.

### **XIII - DATA PROCESSING AND STORAGE OF STUDY-RELATED DOCUMENTS AND DATA**

The documents from a study falling under the scope of the law on biomedical research must be archived by all the parties for a period of 15 years after the end of the study (see GCP, chapter 8: essential documents).

This indexed archive consists of:

- Copies of the AFSSAPS authorisation letter and the mandatory opinion from the Ethics Committee;
- Subsequent versions of the protocol (identified by the version number and date);

- Letters of correspondence with the sponsor;
- The informed consent forms signed by the subjects in a sealed envelope (in the case of minor subjects, these are signed by their parents or guardians) with the corresponding list or enrolment register;
- The complete and validated case report form for each subject enrolled;
- Any specific annexes to the study;
- The final study report from the statistical analysis and the quality control of the study (sent in duplicate to the sponsor);
- Certificates from any audits performed during the course of the study.

The database used for the statistical analysis must also be archived by the head analyst (hard copy or electronic copy).

## **XIV - INSURANCE AND SCIENTIFIC COMMITMENT**

### **XIV.1 - INSURANCE**

Assistance Publique - Hôpitaux de Paris is the sponsor of this study. In accordance with the law on biomedical research studies, it has taken out an insurance policy with the company HDI - GERLING for the full duration of the study, guaranteeing its own civil liability as well as that of any intervening parties (physicians or staff involved in conducting the study) (Law no. 2004-806, Art. L.1121-10 of the French Public Health Code).

Assistance Publique - Hôpitaux de Paris reserves the right to interrupt the study at any given time for medical or administrative reasons. If this occurs, the investigator will be notified.

### **XIV.2 - PRINCIPAL INVESTIGATOR'S COMMITMENT**

Each investigator undertakes to comply with the obligations of the law and to conduct the study in accordance with the GCP guidelines, complying with the principles set forth in the Declaration of Helsinki in force. To this end, a copy of the scientific commitment (DRCD document), dated and signed by the principal investigator of each clinical department of a participating site, will be provided to the sponsor's representative.

A task delegation form will be filled in, dated and signed by all study collaborators.

## **XV - RULES REGARDING PUBLICATION**

AP-HP owns the data and it may not be used or transferred to third parties without AP-HP's prior agreement.

The individuals who actively participated in preparing and implementing the protocol, as well as writing up the results, will be named first in the publications.

Assistance Publique-Hôpitaux de Paris must be mentioned as the sponsor of the biomedical research study and as a provider of funding, where applicable. “Assistance Publique-Hôpitaux de Paris” must appear in the address of the authors.

[figure not shown]

## **XVI - LIST OF ANNEXES**

**Annex 1:** Literature references

**Annex 2:** Investigators and Associate Teams

**Annex 3:** WOMAC Questionnaire Functional Scale

**Annex 4:** MOS SF-12 Quality of life questionnaire

**Annex 5:** Quality of life questionnaire: EQ-5D

**Annex 6:** RAPT (Risk Assessment and Prediction Tool)

**Annex 7:** Multidisciplinary programme procedure: Therapeutic education

**Annex 8:** Multidisciplinary programme procedure: Exercise sessions

**Annex 9:** Pre-TKA self-exercise programme

**Annex 10:** Pedometer use

**Annex 11:** Knee arthroplasty guide

**Annex 12:** Table for Classification of adverse events for a biomedical research study not involving a medicinal product, assimilated product, medical device or genetics

**Annex 13:** Serious adverse event reporting form

## ANNEX 3 – WOMAC QUESTIONNAIRE FUNCTIONAL SCALE

### Function Section

For each of the following activities, please specify the difficulties experienced due to the affected joint, over the past 48 hours.

| How significant is the difficulty you experienced when: | None
0                | Minimal
1             | Moderate
2            | Severe
3              | Very severe
4         |
|---------------------------------------------------------|--------------------------|--------------------------|--------------------------|--------------------------|--------------------------|
| 1. Going down stairs                                    |  |  |  |  |  |
| 2. Going up stairs                                      |  |  |  |  |  |
| 3. Standing up from the seated position                 |  |  |  |  |  |
| 4. Standing                                             |  |  |  |  |  |
| 5. Leaning forward                                      |  |  |  |  |  |
| 6. Walking on level ground                              |  |  |  |  |  |
| 7. Getting in and out of the car                        |  |  |  |  |  |
| 8. Doing the shopping                                   |  |  |  |  |  |
| 9. Putting on tights or socks                           |  |  |  |  |  |
| 10. Getting out of bed                                  |  |  |  |  |  |
| 11. Taking off tights or socks                          |  |  |  |  |  |
| 12. Lying down in bed                                   |  |  |  |  |  |
| 13. Getting in or out of the bath                       |  |  |  |  |  |
| 14. Sitting down                                        |  |  |  |  |  |
| 15. Sitting down on and standing up from the toilet     |  |  |  |  |  |
| 16. Cleaning the house                                  |  |  |  |  |  |
| 17. Carrying out daily housework                        |  |  |  |  |  |

Calculation = (sum/17) x 25

Total 0-100 =

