## **IV.2 - EXCLUSION CRITERIA**

- Institutionalised patients;
- Patients having already undergone ipsilateral total knee arthroplasty;
- Patients with chronic inflammatory arthritis;
- Cognitive or behavioural disorders making the assessment impossible;
- Difficulties in understanding and communicating in French;
- TKA for an indication other than knee osteoarthritis.

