## **VII.1 - VISIT V0 - ENROLMENT VISIT**

The patients selected within the surgical department at Clermont-Ferrand University Hospital and Lariboisière and Cochin hospitals will be contacted by the clinical study technician and, if they are potentially interested in the study, they will be referred to the PMR departments at Cochin and Clermont-Ferrand and the Lariboisière rheumatology department for their enrolment visit and their study follow-up.

At the enrolment visit, the rehabilitation physician or the rheumatologist, with the help of the clinical study technician, will systematically confirm the inclusion and exclusion criteria. The study methods will be clearly explained to the patient. The patient will be given an information sheet and informed consent form. If the patient agrees to take part in the study, he or she will sign the informed consent form.

The following information will be collected in the electronic case report form:

- Demographic parameters (age, sex);
- Socioprofessional parameters (level of studies, profession and professional status (working, on sick leave, on disability, retired));
- Medical examination (weight, height and BMI);
- Inclusion and exclusion criteria;
- Information and consent;
- Demonstration of how to use the pedometer to measure the number of steps taken in the week after the enrolment visit;
- Co-interventions (particularly analgesics and/or NSAIDs, physiotherapy).

Patients will fill in a self-assessment card during the visit, including assessment of the following:

- knee pain over the past 48 hours, assessed using a visual numeric scale from 0 to 100;
- preference regarding hospital discharge destination and RAPT scale (Annex 6);
- function according to the WOMAC scale and the personalised section;
- quality of life (MOS SF-12, Annex 4 and EQ-5D-3L, Annex 5).

The time elapsed between the enrolment visit and the start of the multidisciplinary programme will be no more than one month.

**Randomisation:** patients will be randomised using CleanWeb software.

After randomisation, the patients in the two arms will receive a copy of the Knee Arthroplasty Guide (Annex 11).

The patients randomised into the “standard-treatment” control arm will receive standard medical care.

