### **VII.3.2 - VISITS DURING THE STAY AT THE SURGICAL DEPARTMENT (V2)**

Discharge ability, one of the main endpoints, will be assessed daily by an independent clinical study technician from postoperative D1 until D5 (see section VI-1 of the protocol).

The evaluating physician or clinical study technician will take specific clinical information from the medical file the day before the patient is discharged from the Orthopaedics Department (actual length of stay, rate of transfer to rehabilitation care facilities and adverse events).

After discharge from the Surgical Department, patients will be monitored at consultations, consisting of one visit at 3 months and one at 12 months. These two visits will take place as part of the usual follow-up consultations with the surgeon. Follow-up by post or email, according to the patient's preference, will take place after 6 weeks, 4, 5 and 6 months.

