### **VII.3.3 - CONTACT BY POST OR EMAIL 6 WEEKS AFTER SURGERY**

Patients will fill in a self-assessment card including assessment of the following:

- knee pain over the past 48 hours (numeric scale);
- function according to the WOMAC scale and the personalised section;
- a question on the length of stay at rehabilitation care facilities.

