#### **VII.3.5 - CONTACT BY POST OR EMAIL 4 AND 5 MONTHS AFTER SURGERY**

During the monthly contacts, the WOMAC functional index and personalised section, as well as pain (numeric scale) over the past 48 hours, will be collected from the patient.

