## ANNEX 3 – WOMAC QUESTIONNAIRE FUNCTIONAL SCALE

### Function Section

For each of the following activities, please specify the difficulties experienced due to the affected joint, over the past 48 hours.

| How significant is the difficulty you experienced when: | None
0                | Minimal
1             | Moderate
2            | Severe
3              | Very severe
4         |
|---------------------------------------------------------|--------------------------|--------------------------|--------------------------|--------------------------|--------------------------|
| 1. Going down stairs                                    |  |  |  |  |  |
| 2. Going up stairs                                      |  |  |  |  |  |
| 3. Standing up from the seated position                 |  |  |  |  |  |
| 4. Standing                                             |  |  |  |  |  |
| 5. Leaning forward                                      |  |  |  |  |  |
| 6. Walking on level ground                              |  |  |  |  |  |
| 7. Getting in and out of the car                        |  |  |  |  |  |
| 8. Doing the shopping                                   |  |  |  |  |  |
| 9. Putting on tights or socks                           |  |  |  |  |  |

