## **5.2 Speed of functional recovery**

### **5.2.1 Definition**

The second primary endpoint is the speed of postoperative functional recovery at month 6. This is assessed using the area under the curve of the function subscale of the WOMAC index. The area under the curve will be defined by the trapezoidal rule.

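### The WOMAC form behind the second co-primary endpoint does not say which knee it is about, so patients with both knees affected may score the non-operated one

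*Supplement*

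**What the plan says.** Annex 3 (Function Section) of the latest protocol prints the 17 function items under one instruction: "please specify the difficulties experienced due to the affected joint". It has no field for a side and does not mention the operation. The personalised section uses five of the same 17 items, chosen by the patient.

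The SAP (section 5.2.1) builds a co-primary on this form: "The second primary endpoint is the speed of postoperative functional recovery at month 6", assessed by the area under the WOMAC function curve. Neither 5.2.1 nor 5.2.2 identifies an index knee.

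Protocol section IV.2 has one exclusion tied to a side: "Patients having already undergone ipsilateral total knee arthroplasty". Disease of the other knee is not excluded.

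The study schedule collects the WOMAC at eight points: enrolment, preoperative visit, week 6, months 3, 4, 5, 6 and 12. Section VII.3.2 says: "Follow-up by post or email, according to the patient's preference, will take place after 6 weeks, 4, 5 and 6 months". At week 6, "Patients will fill in a self-assessment card including assessment of the following". At months 4 and 5, "the WOMAC functional index and personalised section, as well as pain (numeric scale) over the past 48 hours, will be collected from the patient". Month 3 may be a consultation, a postal form or a telephone call by the technician, as the patient prefers. None of these sections says which knee is meant. The enrolment list in VII.1 includes neither the side of the planned operation nor the state of the other knee.

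**The concern.** An eligible patient with osteoarthritis in both knees has two candidates for the joint the form asks about. Before surgery both are diseased. Afterwards one has been replaced and the other may still cause difficulty. The wording leaves the choice to the patient, so the reference joint may differ between patients and may change along one patient's curve.

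A score given for the non-operated knee does not measure recovery from this arthroplasty. If the programme acts less on that knee, such scores pull the between-arm difference in AUC towards zero. The personalised WOMAC, a secondary endpoint, uses the same items and has the same weakness. Unless the side and the patient's reading of the question are held somewhere not shown, the analyst cannot tell afterwards which scores are affected.

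**Working it through.** **1. How far the form is completed remotely.** The postoperative points up to month 6 are week 6 and months 3, 4, 5 and 6. Four of these five are by post or email (VII.3.2, VII.3.3, VII.3.5, VII.3.6). Month 3 is at the patient's choice (VII.3.4). The two preoperative forms are completed at visits (VII.1, VII.3.1).

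**2. Reproduce the planned sample size.** Inputs from protocol IX.2: effect size 0.45, power 90%, 2.5% level, Mann-Whitney test, 130 per arm. The SAP (4.1) confirms that tests are two-sided.

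- Two means, per arm: n = 2(z₀.₉₈₇₅ + z₀.₉₀)² / 0.45² = 2(2.241 + 1.282)² / 0.2025 ≈ 122.6, so 123.
- Divide by the Mann-Whitney relative efficiency under normality, 3/π = 0.955: 123 / 0.955 = 128.8, so 129. The plan states 130.
- Power at 130 per arm: Φ(0.45 × √(130/2) × √(3/π) − 2.241) = Φ(1.304) = 0.904.

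The planned figure reproduces.

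**3. Effect of wrong-knee scores.** Let q be the share of scores that refer to the other knee, and c the fraction of the programme effect that those scores still carry. With the SD unchanged, the effective effect size is 0.45 × [1 − q(1 − c)]. Power follows from the formula in step 2. Neither q nor c is in the documents; both are assumptions.

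| q | c | effect size | power, 130 per arm | n per arm for 90% |
|---|---|---|---|---|
| 0 | – | 0.450 | 90.4% | 129 |
| 5% | 0 | 0.428 | 87.0% | 143 |
| 10% | 0 | 0.405 | 82.9% | 160 |
| 5% | ½ | 0.439 | 88.8% | – |
| 10% | ½ | 0.428 | 87.0% | 143 |

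The last row equals the second because 10% × ½ = 5%.

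**4. Check against the SAP's analysis.** Section 5.2.2 compares AUCs with a linear mixed model adjusted for centre and surgeon, not with the Mann-Whitney test. A t-test approximation at 130 per arm gives 91.7% with no wrong-knee scores, and 88.6% and 84.7% at q = 5% and 10% with c = 0. The loss is of the same order.

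**The case against.** Much can be said on the other side.

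- **The form patients read is not shown.** Participants must communicate in French, and the annex is in English. The self-assessment cards and the eCRF are not reproduced. A card might name the knee, and the eCRF might hold the side. This stands as a limit. Even so, the printed annex is the plan's specification of the questionnaire, and it leaves the point open.
- **The operated knee is a likely reading.** The instruction uses the singular, and patients are contacted at intervals counted from their operation. A reader might infer that after surgery the remaining arthritic knee is what most patients would score. Nothing in the documents supports that. The claim is only that some patients may do so.
- **Staff are present at the preoperative forms.** Enrolment and the preoperative assessment are visits, and eligibility has just been confirmed for a scheduled arthroplasty. This lessens the ambiguity before surgery, but not at the remote points afterwards.
- **The pain item may be sound.** The protocol lists "knee pain over the past 48 hours, assessed using a visual numeric scale from 0 to 100" as card content, but the item itself is not printed. A reader might infer the same fault there; its wording is unknown, so it can only be checked.
- **Large losses of power need stacked assumptions.** If 50% of patients had a symptomatic other knee, half of them answered for it and the programme did nothing for it, 25% of scores would be affected and power would be about 66%. None of these three figures is documented. The third fits poorly with a programme of lower-limb strengthening, balance and walking exercise (VII.2). That figure should not be used as an estimate.
- **There is no mechanism for bias between arms.** The form is the same in both arms of a randomised trial. This stands in full.

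**Conclusion.** The point holds as a risk of avoidable measurement noise in a co-primary endpoint and in the personalised WOMAC. Three facts are on the page: the instruction names no index knee, patients with both knees affected are eligible, and most postoperative forms up to month 6 are completed remotely.

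The size cannot be taken from the documents. For an assumed 5-10% of scores given for the other knee, power falls from about 90% to about 87-83% with no effect on that knee, or about 89-87% with half the effect. These figures rest on a Mann-Whitney approximation, an unchanged SD and a programme effect that is smaller on the other knee. If the programme helped both knees equally, the between-arm difference would not shrink for this reason.

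A reader might go further and conclude that the AUC comparison is biased towards one arm or is invalid. The documents support neither. This is a low-cost improvement to the form, not a flaw that undermines the design.

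**What to change.** On the WOMAC form at every time point, replace the unspecified joint with *the knee that is to be / has been operated on in this study*, with the side pre-filled. Use the same phrase in the postal, email and telephone instructions. Record the side at V0 if the eCRF does not already hold it. Check that the 48-hour pain item names the same knee. Recording the state of the other knee at baseline would also allow a sensitivity analysis by that variable.

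If data have already been collected, report the ambiguity as a limitation, and run that sensitivity analysis only if the state of the other knee was recorded.

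The cost is one line of wording, one pre-filled field and, if adopted, one baseline item. There are no extra visits, and no planned sample-size figure changes. The downside is a small change to the instruction line of a named questionnaire, so it must be applied identically in both arms and at all time points.
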